## **Assessment Procedures**

### Telephone Survey

Response rates in telephone surveys are increased by the use of both an advance letter and monetary incentive; both will be used. Individuals with cognitive impairment or limited English proficiency for a telephone interview will not undergo interview. Interviewers conduct a 20-minute survey using computer-assisted telephone interview (CATI) methodology as previously described.

Eligibility questions will evaluate whether current depression is absent and exclude subjects who answer affirmatively to the following two screening question: 1) Are you depressed nearly every day for two weeks or more; 2) Have you lost interest in normal activities nearly every day for two weeks or more. Absence of depression will

also be evaluated by the 10-item Center for Epidemiologic Studies Depression score < 4. If subjects do not evidence symptoms of current depression, they will be advanced to interview assessment, in which the SCID interview will be administered to confirm the absence of current depression., and depression within the last year, using DSM-IV or after 2013 using DSM-5 diagnostic criteria.

As the PSQI will be administered to determine the presence of sleep disturbance; those with minimal sleep complaints, as defined by PSQI scores  $\leq 5$  are excluded for further eligibility assessment.

#### In person interview assessment

The Informed Consent is reviewed with questions addressed. In a face-to-face interview format lasting about 120 minutes, we assess the following domains: (1) Absence of depression within the last 12 months by administration of the SCID; (2) Presence of insomnia disorder with administration of the SCID-IV and Duke Structured Interview for Sleep Disorders (DSISD) to identify ICSD-2 and DSM-IV insomnia, and absence of other sleep disorder diagnoses; (3) demographic information and medical / medication histories; (4) health status; and (5) psychosocial stress and social support. To assess inflammatory cytokine activity, blood samples will be collected by venipuncture.

#### Post-treatment and follow-up assessments

After post-treatment, we will monitor monthly depressive symptom severity and possible depression incidence using an ATRS to administer the PHQ-9. If a subject reports moderate depressive symptoms ( $\text{PHQ-9} \geq 10$ ), subjects will undergo an interview assessment with the SCID to determine whether a major depressive episode has occurred. In addition, scheduled follow-up assessments lasting about 60 minutes will be conducted at 6 months intervals over the two year period with an extension to three

years, with evaluation of interval changes for interview and questionnaire measures, as well as inflammatory cytokine activity. The SCID interview will be administered every 6 months to determine whether a depression has occurred. We will provide financial incentives at each follow-up, obtain contact information for someone who does not live with the participant, and mail newsletters and birthday cards to forwarding addresses requested. One month before follow-up, subjects will receive a letter confirming the visit; one week before, study personnel will telephone subjects and remind them of the visit and/or reschedule to another date. In our large-scale study of older adults, similar procedures have yielded robust follow-up completion rates (>97%). At the end of each visit, next follow-up will be scheduled.

## **Outcomes**

### Depression assessment

Incidence of a major depression diagnosis constitutes the primary outcome, and only those subjects who are not depressed for at least 12 months will be included for entry.

During eligibility assessment, we will exclude those older adults who fulfill screening criteria for depression (i.e., 10-item Center for Epidemiologic Studies for Depression  $\geq 4$ ). Absence of depression will be confirmed by administration of the *Structured Clinical Interview for DSM-IV or DSM-5*. This interview will also diagnose a lifetime history of major or minor depressive disorder and/or psychiatric conditions, as well as to relevant clinical data about number of episodes, age of onset, last episode, and treatment variables. Severity of depressive symptoms will be evaluated with the PHQ-9. The PHQ-9 scores each of the 9 criteria for major depressive disorder in the Diagnostic and Statistical Manual (Fourth Edition, Text Revision [DSM-IV-TR], with as “0” (not at all) to “3” (nearly every day); maximum score of 27. Because all eligible

participants will report sleep disturbance at entry, baseline data will use the PHQ-8, which is scored for each of the criteria for major depressive disorder with the exception of insomnia, yielding a maximum score of 24. Scores below 5 on the PHQ-9 indicate none to minimal depression; and scores below 4 on the PHQ-8 indicate none to minimal depression.

During follow-up, depressive symptom severity will be assessed by the PHQ-9 to capture depressive symptoms between 6 months assessment. As noted, ATRS monitoring of depression with the PHQ-9 will be used to identify possible depression incidence in the interval between depression. If a possible case of depression is detected by the PHQ-9, the participant will be scheduled for an additional assessment, separate from the routine 6 months assessment. At this assessment, as well as all 6 months assessment, the SCID interview will be used to diagnose a major depressive episode, as well as gather information about time of onset and possible treatment history. For subjects who receive a major depression diagnosis, information is provided so that they can obtain treatment of their depression. Whether such treatment was obtained is evaluated at subsequent follow-up assessments. Weekly consensus meetings are used to maintain reliability and criterion validity in the diagnosis of depression. Credentials of individuals who attend consensus meetings include board-certified psychiatrists, board certified clinical psychologists, and psychiatry residents, psychology interns and post-doctoral fellows. Regular viewing and scoring of videotaped interviews is implemented to assess reliability. We have chosen this method over the “test-retest” method in which the same subject is interviewed twice for several reasons. The test-retest method is very labor intensive. Furthermore, test-retest examines the ability of different interviewers to obtain information, but is affected by the reliability of the patient in giving the same answers each time as well as by practice effects. Our focus is on the reliability with which our interviewers decide whether a

patient's answer meets threshold for the given item. Quarterly reliability monitoring will allow for the early detection of problems. Inter-rater reliability was consistently maintained at >95% for scoring of threshold criteria for major depressive disorder, as well as insomnia disorder. All modules of the SCID are administered.

#### Insomnia assessment

The secondary outcome of this study is remission of insomnia disorder as defined by DSM-5 diagnostic criteria. Sustained remission of insomnia was defined by the absence of insomnia by DSM-5 diagnostic criteria at each of the assessments for the duration of the study. Repeated evaluation at each assessment will confirm that remission of insomnia complaints is durably maintained consistent with the duration criteria for DSM-5 insomnia disorder. Remission of insomnia disorder over the duration of the study will be evaluated by examining whether remission of insomnia complaints and remission of insomnia disorder is continuously sustained over repeated assessment intervals.

At baseline and follow-up, use of sedative hypnotic medication will be tracked, although we have preliminarily found that such use does not mitigate the risk profile of sleep disturbance on depression incidence. In contrast to the PSQI, the AIS and scoring of insomnia severity is not confounded by scoring of items related to sleep apnea and sedative hypnotic use.

A self-report questionnaire such as the PSQI or AIS can be readily used in primary care and collaborative care setting to assess the presence of sleep disturbance for delivery of an intervention to treat insomnia and prevent depression. Hence, in contrast to insomnia treatment studies in which the primary outcome is the sleep domain, objective measures of sleep such as polysomnography (PSG) are not being obtained. Prior insomnia treatment trials have demonstrated that insomnia response and remission occurs even in the absence of significant changes in objective measures of PSG sleep

(e.g., two nights in the sleep laboratory) period of assessment of sleep. In a subgroup of the sample, actigraphy measures will be obtained.

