Manual for Mental Disorders, fourth edition (DSM-IV). In addition to the Structured Clinical Interview for DSM-IV, the Duke Structured Interview for Sleep Disorders (DSISD) will be administered to acquire diagnostic criteria data to ascertain the presence of insomnia using ICSD-2 and DSM-IV criteria.

After 2013, DSM-5 criteria were used to assess the presence of insomnia disorder, including the revised duration criterion for diagnosis of insomnia. Specifically, Diagnostic and Statistical Manual (DSM)–IV criteria specified duration at one month for insomnia; International Classification of Sleep Disorders (ICSD)-2 did not specify duration for insomnia. DSM-5 specified duration criteria of 3 months for insomnia disorder, and in 2014, ICSD-3 specified 3 months duration for insomnia disorder. Because the study had already enrolled subjects prior to publication of DSM-5, inclusion criteria used presence of screening eligibility of PSQI > 5 with confirmation of insomnia disorder by DSM-IV and ICSD-2 diagnostic criteria. However, all participants were also diagnosed with DSM-5 and ICSD-3 criteria including the revised duration criterion to 3 months, with subgroup analysis (See Statistical Plan).

In addition to identifying those older adults with insomnia, older adults with evidence of depression will be excluded from study entry. Along with eligibility evaluation with the PSQI, community dwelling adults will be evaluated with the 10-item Center for Epidemiologic Studies Depression (CES-D) score and will have CES-D score < 4. For those older who are eligible for entry, the absence of major depression currently, and for at least one year prior to entry, will be confirmed using Structured Clinical Interview (SCID) for DSM-IV. After 2013, the absence of major depression used DSM-5 criteria. In addition to the absence of current depression, participants were excluded if a major depression was diagnosed in last 12 months. Severity of depressive symptoms is evaluated using the Patient Health Questionnaire (PHQ-9). We have previously found that older adults with insomnia who 10-item CES-D scores <4, and also do not have

current or recent history of major depression typically show minimal to mild depressive symptoms with PHQ-9 scores  $\leq 10$ .

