### **Eligibility Criteria**

#### Inclusion Criteria:

Participants must:

- 1) Be older adults > 60 year of age
- 2) Report sleep disturbance with PSQI > 5, with confirmation of insomnia diagnosis as determined by ICSD-2 and DSM-IV criteria

Among those eligible with PSQI > 5, severity and diagnostic criteria will be employed to confirm the presence of insomnia. Diagnostic interview data will be obtained by the SCID and by Duke Structured Interview for Sleep Disorders (DSISD) to ascertain the presence of insomnia using ICSD-2 and DSM-IV criteria. In our studies of older adults and other populations, we have found that PSQI > 5 corresponds to insomnia diagnosis using ICSD-2 and DSM-IV with >99% agreement with the exception of the duration of insomnia criterion, consistent with the reported 98.7% sensitivity of the PSQI to detect DSM-IV insomnia. As noted, after 2013, DSM-5 criteria will be used to diagnose insomnia disorder. However, the duration criteria for DSM-IV insomnia disorder will be maintained, and DSM-IV insomnia disorder is an inclusion criteria.

Additional considerations for inclusion are the following. Those with and without prior history of depression will be included if the depression did not

occur within the last 12 months. This information will be obtained by administration of the SCID interview. Those with history of depression will be included because it is estimated about 30% of those with sleep disturbance will have such a prior history.

Since we estimate about 30% of those with insomnia will have a history of depression, subjects will be allowed to continue antidepressant treatment during the administration of the behavioral intervention for insomnia. We do not believe that ongoing treatment with an antidepressant medication will substantially alter the relationship between insomnia and depression incidence (i.e., depression recurrence) in older adults with a history of depression, because we previously found in our longitudinal prospective cohort study that neither use of antidepressant medications nor sedative/hypnotic medications protected from the risk of depression recurrence in those subjects who had sleep disturbance and a history of depression. Hence the rationale for this study: to treat insomnia to prevent depression taking into account ongoing antidepressant medication treatments. This strategy increases the generalizability of the results.

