As noted, DSM diagnostic criteria for insomnia were revised with the duration criterion revised from one month in Diagnostic and Statistical Manual (DSM)–IV to three months in DSM-5. Duration criteria were unspecified in ICSD-2 and specified as 3 months for insomnia disorder in ICSD-3. Eligibility criteria at the onset of the study used insomnia diagnostic criteria as specified DSM-IV and ICSD-2 criteria, and these criteria for inclusion were maintained for the study duration. Hence, it was possible that some enrolled participants did not meet insomnia

diagnostic criteria for DSM-5. To address this possibility, all diagnostic interview data were reviewed for subjects and consensus diagnosis was performed to determine diagnosis using DSM-5 criteria for insomnia disorder, as well as major depressive disorder. Whereas all participants in the enrolled sample met DSM-IV and ICSD-2 criteria for insomnia, some did not meet DSM-5 and ICSD-3 criteria for insomnia disorder. Hence, a post-hoc analysis of the primary outcome was conducted in the subsample who were found to have insomnia disorder at entry as defined by DSM-5.

Exploratory analysis were also performed to assess the survival benefit based on subgroups of interest related to the risk depression incidence as noted in the adjusted model. We estimated treatment effect for each subgroup. Particular subgroups of interest were based on our preliminary findings as noted above including age, sex, medical co-morbidity, use of sleep medications, depression history, use of anti-depressant medications.

For the secondary categorical outcome of remission of insomnia, differences in relative proportions achieved at post-intervention and sustained up to 36 months were tested using mixed regression models adjusting for the above set of covariates.

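### Remission means absence of DSM-5 insomnia, but entry needs only DSM-IV/ICSD-2 insomnia, so some participants meet the remission definition at baseline and may still do so at post-treatment without true remission

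*Supplement*

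**What the plan says.** Entry (final protocol, Inclusion Criteria) is PSQI above 5 "with confirmation of insomnia diagnosis as determined by ICSD-2 and DSM-IV criteria". After DSM-5 appeared, "the duration criteria for DSM-IV insomnia disorder will be maintained, and DSM-IV insomnia disorder is an inclusion criteria".

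The two systems differ in duration. Under Design Overview, DSM-IV "criteria specified duration at one month for insomnia", ICSD-2 gave no duration, and "DSM-5 specified duration criteria of 3 months for insomnia disorder".

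The outcome (final protocol, Insomnia assessment) follows the newer system: "The secondary outcome of this study is remission of insomnia disorder as defined by DSM-5 diagnostic criteria". The durable form does too: "Sustained remission of insomnia was defined by the absence of insomnia by DSM-5 diagnostic criteria at each of the assessments". Neither sentence requires that DSM-5 insomnia was present at baseline. The same section also says that remission of complaints and remission of the disorder will both be examined across visits, without saying how the two combine.

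The final SAP (Statistical analysis) acknowledges that everyone enrolled met the DSM-IV and ICSD-2 definitions, but "some did not meet DSM-5 and ICSD-3 criteria for insomnia disorder". Its response is a post-hoc analysis of the primary outcome, incident depression, in those with DSM-5 insomnia at entry. The mixed models for remission, at post-intervention and sustained to 36 months, carry no such restriction. Nor does the Cox model of time to depression that stratifies the arms by sustained remission, with unremitted SET participants as the reference.

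**The concern.** Remission should mean that a condition present at baseline has gone. Here the condition that must be absent (DSM-5 insomnia) is not the one that had to be present (DSM-IV/ICSD-2 insomnia). A participant without DSM-5 insomnia at entry meets the remission definition before treatment starts.

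The SAP saw that the change of criteria mattered, but addressed it only for depression, an outcome whose definition does not involve insomnia status. The outcome that depends directly on DSM-5 insomnia has no scoring rule and no sensitivity analysis.

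At stake are the meaning of the post-intervention remission rates and, to a lesser degree, the make-up of the strata in the remission-stratified Cox model.

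**Working it through.** **Inputs**

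- Durations of one month (DSM-IV) and three months (DSM-5): protocol, Design Overview.
- Treatment of 8 weeks: protocol, Interventions.
- Expected remission of about 50% (CBT-I) and 10% (SET): protocol, Design Overview, where no time point is attached.
- 125 per group, power above 90%, two-sided 5%, intraclass correlation 0.01: final SAP, Sample size.
- Share *f* without DSM-5 insomnia at entry: not given. I assume 5, 10 and 20%, with 30% as an extreme for power.

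**1. The plan's own figure.** Comparing 10% with 50% at 125 per group gives power above 99.9%; 26 per group would give 90% (31 with continuity correction). For treatment groups of 5 to 10, the design effect 1 + (m − 1) × 0.01 is 1.04 to 1.09, and power stays above 99.9%. The stated bound is met.

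**2. Duration with continuous, unchanged symptoms.**

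- 8 weeks = 56 / 30.44 = 1.84 months.
- Shortest possible duration at end of treatment: 1 + 1.84 = 2.84 months, just under three.
- Entry durations that still fall short there: below 3 − 1.84 = 1.16 months. Any wait before the first session or after the last lowers this limit.
- At the first 6-month visit: at least 1 + 6 = 7 months if visits are counted from entry, and more if counted from post-treatment.

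So an unchanged participant lacks DSM-5 insomnia at baseline, may lack it at post-treatment if entry duration was very short, and has it by the first 6-month visit.

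**3. A break in symptoms.** The documents do not say whether follow-up duration counts the current episode. If it does, insomnia that lifted after treatment began and then returned has lasted less than 1.84 months at post-treatment. It cannot meet three months, whatever the entry diagnosis. At later visits a relapse less than three months old would also be missed, unless remission of complaints is required too.

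**4. Upper bound at post-treatment for the entry mismatch.** If everyone in *f* is scored as remitted, measured remission is f + (1 − f) × r, and the difference is (1 − f) × 40 points.

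| f | CBT-I | SET | Difference (points) | Ratio | f as share of SET remitters |
|---|---|---|---|---|---|
| 0 | 50% | 10% | 40 | 5.0 | 0 |
| 5% | 52.5% | 14.5% | 38 | 3.6 | 0.05/0.145 = 34% |
| 10% | 55% | 19% | 36 | 2.9 | 0.10/0.19 = 53% |
| 20% | 60% | 28% | 32 | 2.1 | 0.20/0.28 = 71% |

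Step 2 shows why these are bounds: only the part of *f* with very short entry duration can still lack DSM-5 insomnia at post-treatment if symptoms continue unchanged. The route in step 3 is separate, and the documents give nothing to size it with.

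**5. Power under the bound.** At 125 per group it stays above 99.9% for *f* up to 20%. At 30% (65% versus 37%) it is 99.5%.

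**6. Unequal shares.** With *f* of 15% in SET and 5% in CBT-I, the rates are 23.5% and 52.5%, a difference of 29 points. With the shares reversed they are 14.5% and 57.5%, a difference of 43 points. Imbalance can therefore push the difference either way, so the number by arm is needed.

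**The case against.** The strongest defence has four parts.

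- **The choice is disclosed and reasonable.** DSM-5 appeared mid-trial. Holding entry constant while reporting the outcome by the current standard can be defended. This stands, but it does not supply the missing rule for participants who were not DSM-5 cases at baseline.
- **Time closes the gap.** Duration is the only difference that the documents describe, and persistent insomnia soon passes three months. This stands, and it limits the problem mainly to the post-treatment visit.
- **Complaints are assessed as well as the diagnosis.** The protocol does say this, and a renewed complaint would count against remission if that clause governs. The text does not say that it does; the outcome sentence names only the disorder.
- **It is a secondary outcome.** The primary Cox comparison does not use remission, and a balanced share pulls the remission difference towards zero. This stands and lowers the priority.

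A reader might infer something stronger: that these participants never had DSM-5 insomnia and so count as remitted through 36 months without any change. The documents do not support that. The SAP speaks of status at entry, and sustained remission requires absence of DSM-5 insomnia at every assessment, which continuous insomnia fails by the first 6-month visit. The stronger reading would need a criterion other than duration to be unmet, and no such criterion is mentioned.

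**Conclusion.** The concern holds in a limited form. Entry and remission use different diagnoses, some participants satisfy the remission definition at baseline, and the plan gives no rule for them in either remission analysis.

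The exposure is mainly at the post-intervention comparison. With continuous symptoms it reaches only those whose insomnia had lasted less than about 1.2 months at entry. It reaches further if duration is counted from the start of the current episode. Remission sustained to 36 months is largely unaffected. The exception is a participant for whom post-treatment is the only visit before a depression event or dropout; through such cases some misclassification can enter the strata of the Cox model, including its reference group.

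The figures of 52.5 versus 14.5, 55 versus 19 and 60 versus 28 are upper bounds for the post-treatment visit under assumed shares of 5, 10 and 20%. They are not expected results and should not be applied to sustained remission. The issue is the validity of the outcome; power above 90% is secure.

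**What to change.** 1. Report by arm how many participants lacked DSM-5 insomnia at entry, and which criterion was unmet.
2. Analyse DSM-5 remission, and the remission-stratified Cox model, in participants with DSM-5 insomnia at baseline. As an alternative or in addition, score remission in all participants against the entry criterion: DSM-IV/ICSD-2 insomnia with its one-month duration. That criterion is not the same as DSM-5 with the duration rule removed.
3. State how duration is counted at follow-up after a break in symptoms.
4. Require remission of complaints as well as of the disorder, so that a recent relapse is not scored as remission.

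The cost is SAP wording and re-coding of interview data already collected. The SAP says that all diagnostic interviews were reviewed and given DSM-5 consensus diagnoses, so the affected participants can be identified. The downsides are lower remission rates and a slightly smaller sample in the restricted analyses.
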